### Participants

Patients insured under the statutory health insurance and with objectified HF with reduced left ventricular ejection fraction (LVEF ≤ 40%) are identified consecutively in the participating CP or their cooperating GP practices. After initial consultation and trial information by the cardiologist or GP, eligibility confirmation, consent, and enrollment are completed at the CP. In intervention clusters, the HF-MPA assumes responsibility for patient care under delegation. Patients with advanced cognitive impairment or without telephone access were excluded.

### Development of the intervention program

The intervention integrates five synergistic elements. First, evidence-based HF care is implemented in each practice, focusing on patient safety, adherence, and optimization of pharmacotherapy. Second, non-physician staff receive a structured, certified curriculum (HeartNetCare™ [10] provided by the German Society of Cardiology (DGK)) through which they gain qualifications in patient education and symptom monitoring. The training curriculum contents are presented in Supplementary Table S2. Completing the curriculum yields a HF-MPA certificate. Third, an eHealth platform (medPower®; ISO-certified medical product) is deployed, allowing HF-MPAs, cardiologists, and GPs to record, share, and act on clinical data in real time. Fourth, portable telemedical devices (e.g., blood pressure monitors and body weight scales) are provided to enable patient-specific telemonitoring and to ensure timely recognition of clinical deterioration by conducting a preliminary assessment of the collected data based on medically defined and individually set thresholds. Finally, structured communication pathways among cardiologists, GPs, and HF-MPAs ensure coordinated care; HF-MPAs perform scheduled telephone follow-ups, document symptoms and vital signs, and consult the supervising cardiologist or GP when warning signs emerge.

### Role of the HF-MPA

The HF-MPA is employed in the CP and works under the delegation principle. The HF-MPA provides structured contact at program start, conducts scheduled telephone follow-ups and telemonitoring according to patient needs and disease severity, and promptly escalates warning signs. In consultation with the cardiologist, the HF-MPA collaborates with the GP to identify clinical concerns, to implement therapy adjustments and to optimize guideline-concordant medication, when abnormalities are identified. Figure 1 shows the patient pathway and the distribution of patient groups. The HF-MPA is also responsible for documenting care-relevant information using the patient-specific electronic case file of the eHealth-platform. The eHealth-platform is accessible to the patient’s cardiologist, responsible HF-MPA, and the GP, with the contents of the dashboard displayed according to the assigned role and corresponding permissions. The platform is designed to enhance inter-professional and cross-sectoral care coordination and facilitates timely (tele-)monitoring of patients.

**Fig. 1 Fig1:**
[figure not shown]
Study flow for control and intervention group

### Outcomes

The primary endpoint is the change in HF-specific QoL from baseline to 12 months, measured with the 23-item Kansas City Cardiomyopathy Questionnaire Overall Summary Score (KCCQ-OSS). Its German version has been validated at the Comprehensive Heart Failure Center Würzburg [19]; telephone administration reliability was evaluated prior to the start of the study [20]. The secondary endpoints are presented in Table 1 and include HF-related hospitalization (adjudicated from medical reports) and a health-economic evaluation of first-year intervention costs.

**Table 1 Tab1:** Secondary endpoints in the HI-PLUS trial

• Composite of unplanned hospitalization due to heart failure (HF) and all-cause mortality
• Components of this composite
• Changes over time in the following parameters:
• Kansas City Cardiomyopathy Questionnaire (KCCQ) Total Symptom Score (KCCQ-TSS)
• KCCQ Clinical Summary Score (KCCQ-CSS)
• Patient Health Questionnaire-9 (PHQ-9)
• Generalized Anxiety Disorder-7 (GAD-7)
• EuroQol-5D-5L
• Montreal Cognitive Assessment (MoCA) test
• New York Heart Association (NYHA) class
• Glomerular filtration rate
• N-terminal pro-B-type natriuretic peptide (NT-proBNP) levels
• Incidental costs in the first year of the intervention through HI-PLUS (health economic project evaluation)
• Acceptance of the new care model
• The previously named quality indicators of the planned Disease Management Program Herzinsuffizienz (DMP-HI) (according to the current planning status of the DMP-HI):
1. Proportion of participants with eGFR and serum electrolytes measured at least every 6 months, relative to all participants with at least 6 months of follow-up 2. Proportion of participants receiving a combination of at least two prognostic agents 3. For participants who were untrained at the time of enrolment: Proportion of participants who attended a recommended training program 4. Proportion of participants with unplanned hospitalization for HF in the previous 12 months, based on all participants with at least 12 months of participation 5. For participants with NYHA Class I-III who were able to exercise: proportion of participants who regularly exercised 6. For participants on Angiotensin-Converting-Enzyme (ACE) inhibitors or angiotensin receptor blockers (ARBs): proportion of participants reaching target dose or maximum tolerated dose 7. For participants taking beta-blockers: proportion of participants reaching the target dose or maximum tolerated dose 8. For participants on mineralocorticoid receptor antagonist (MRA): proportion of participants who reached the target dose or maximum tolerated dose

*HF* heart failure, *KCCQ* Kansas City Cardiomyopathy Questionnaire, *PHQ-9* Patient Health Questionnaire-9, *GAD-7* Generalized Anxiety Disorder-7, *MoCA* Montreal Cognitive Assessment, *NYHA* New York Heart Association, *NT-proBNP* N-terminal pro-B-type natriuretic peptide, *DMP-HI* Disease Management Program Herzinsuffizienz, *eGFR* estimated global filtration rate, *ACE* Angiotensin-Converting-Enzyme, *ARBs* angiotensin receptor blockers, *MRA* mineralocorticoid receptor antagonist

### Data collection

At enrollment, targeted phenotyping captures information on socio-demographic determinants and care situation of patients, as well as HF type and severity, previous history of cardiac disease, comorbid conditions, and current medications. CP teams enter endpoint-relevant information into the study database at baseline and 12 months. Additionally, patients are interviewed by telephone by trained staff to collect endpoints at baseline and 12 months. Quality of care provided to patients is evaluated through the administration of the Patient Assessment of Chronic Illness Care measure (PACIC-5A) at enrollment and the final visit. Furthermore, a qualitative study will be conducted among cardiologists, HF-MPAs, general practitioners, and patients to assess the quality of implementation as well as expectations associated with and acceptance of the innovative care pathway. Study data are managed in REDCap© electronic data capture tools hosted at the University of Würzburg [21, 22]. In the intervention group, care-relevant information is also documented with the eHealth platform. Data monitoring is performed by the Clinical Trial Centre of the University Hospital Würzburg.

### Sample size

The trial is powered to detect a 5-point between-group difference in KCCQ-OSS from baseline to 12 months, a threshold regarded as clinically meaningful and associated with a 10% risk reduction in mortality and HF-related rehospitalization [4, 23–25]. Similar or even greater improvements have been observed in previous therapy optimization studies [26]. The sample size calculation is based on a two-sided *t*-test with degrees of freedom based on the number of clusters, with the significance level set at 5%.

In the INH study, an intraclass correlation coefficient (ICC) of 0.003 was reported for the change in KCCQ-OSS between baseline and 12-month follow-up [10]. Given that the clusters in the INH study comprised cardiology departments within one region, we assume a more conservative ICC of 0.01 for the current trial. For estimating the KCCQ-OSS standard deviation (SD), we refer to the study by Jayaram, which reported an SD of 25.4 points for the change over 6 months [26]. Since the SD remained relatively stable during this period, we assume an SD of 25.4 points after 12 months as well. We also assume a variation in the number of patients per cluster of 0.5. With an ICC of 0.01, an average of 21 HF patients per cluster (*n* = 1050) is needed to detect a significant 5-point difference with 80% power. Considering an expected dropout rate of 20% for patients and 10% for practices, the final sample size is 56 clusters with 1350 patients. Each cardiologist is expected to collaborate with 2–5 GPs, involving up to 280 GPs in total. The sample size was conducted using the software PASS 2020.

### Statistical methods

Analyses will follow the intention-to-treat principle using SAS 9.3 or R. The significance level is defined at 5%. Descriptive analyses of the primary and secondary endpoints will be carried out. The primary analysis will use a univariable linear mixed-effects model with random effects for clusters (CPs) and fixed effects for group (intervention vs control). A multivariable mixed-effects model will secondarily adjust for potential confounders, e.g., age, sex, NYHA functional class, time since diagnosis, care dependency, and living status. A predefined sensitivity analysis will be performed to account for the timing of the anticipated DMP-HI implementation, whose exact start date had not been determined at the time of trial approval. Specifically, a mixed-effects model will be applied to the primary outcome, including both groups and duration of DMP-HI use as fixed effects, while modelling CP as a random effect. If a CP has not participated in the DMP-HI by the end of data collection, duration will be set to zero. If no CP has adopted the DMP-HI 4 weeks before study end, this analysis will be omitted. In addition, a subgroup analysis will evaluate the primary endpoint based on the presence/absence of a trained HF-MPA prior to trial start. Analyses of secondary outcomes will be conducted using univariable and multivariable mixed-effects models. To assess the potential influence of GPs on study outcomes, an additional sensitivity analysis will be run to account for clustering effects at the GP level. This will involve the use of a mixed-effects model with the intervention as a fixed effect and both cardiologists and GPs as random effects.

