## Results

The study aims to recruit 1350 patients (2 × 675) in 56 CPs in Germany and follow them for 12 months. The start-up phase started in October 2022; recruitment started in June 2023 and was concluded in June 2025. The last follow-up visit will take place in June 2026. The study will report in September 2026.

Of 1480 cardiologists contacted, 237 cardiologists from 145 CPs expressed interest to participate; 116 CPs received contracts, and 55 CPs (28 intervention and 27 control sites) were ultimately enrolled (Fig. 2). Group allocation takes place after the contract has been signed. Seven CPs (four from the intervention group and three from the control group) withdrew their participation from the trial. None of the CPs had started recruiting patients yet, and the reason for their withdrawal was a shortage of staff or time. All sites received training on recruitment, use of the electronic case report forms (eCRF), and questionnaires. Intervention CPs as well as the certified HF-MPA received additional training on the eHealth platform. The HF-MPA of intervention CPs received specialized HF training according to the curriculum certified by the German Cardiac Society that is based on the evidence-based HeartNetCare™ concept [10].

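### The primary model compares change in KCCQ-OSS without baseline KCCQ-OSS as a covariate: the stated 80% power is met, but precision available at no data cost is given up

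*Protocol article*

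**What the plan says.** Under Outcomes, the article defines the endpoint: "The primary endpoint is the change in HF-specific QoL from baseline to 12 months", measured by KCCQ-OSS. Under Statistical methods, the primary analysis is a "univariable linear mixed-effects model with random effects for clusters (CPs) and fixed effects for group (intervention vs control"). The word univariable leaves no room for a baseline covariate, so this is a stated choice and not a detail left to an analysis plan.

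The covariate is available. Under Data collection, "patients are interviewed by telephone by trained staff to collect endpoints at baseline and 12 months".

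A second, adjusted model is planned: "A multivariable mixed-effects model will secondarily adjust for potential confounders, e.g., age, sex, NYHA functional class, time since diagnosis, care dependency, and living status". Baseline KCCQ-OSS is not among the examples, but the list is openly non-exhaustive.

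On the order of events, Results says: "Group allocation takes place after the contract has been signed". Of seven practices that withdrew after being assigned to an arm, it says: "None of the CPs had started recruiting patients yet". Under Participants, patients are identified consecutively, and "eligibility confirmation, consent, and enrollment are completed at the CP". Patient recruitment therefore appears to follow allocation. The article does not say whether patient identification was masked.

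**The concern.** A change score subtracts the whole baseline value, which fixes the slope of the 12-month score on baseline at 1. When the true slope is below 1, this leaves avoidable noise in the outcome and over-corrects any chance difference in baseline between arms. A model with baseline as a covariate estimates the slope instead.

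Two things are at stake. The first is the width of the confidence interval for the primary effect in a trial sized at 80% power. The second is how far a chance imbalance in baseline KCCQ-OSS would move the estimate relative to the 5-point target.

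**Working it through.** **Inputs from the article (Sample size):** target difference 5 points; SD of change 25.4; ICC 0.01; cluster-size variation 0.5, read as a coefficient of variation; 21 patients per cluster and n = 1050, hence 50 clusters and 525 patients per arm; two-sided 5%; t-test with cluster-based degrees of freedom, here 50 − 2 = 48.

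**Input not in the article:** r, the correlation between baseline and 12-month KCCQ-OSS. It is assumed over 0.3 to 0.9.

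**Step 1: reproduce the plan.**
- Design effect = 1 + ((0.5² + 1) × 21 − 1) × 0.01 = 1.2525.
- SE = 25.4 × √(2/525 × 1.2525) = 1.754.
- Non-centrality = 5/1.754 = 2.85. The non-central t with 48 df gives power of 79.7%. A relative-efficiency form of the design effect (1.245) gives 80.0%. The stated 80% is confirmed.

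**Step 2: variance with baseline as covariate.** With score SD σ at both times:
- Var(change) = 2σ²(1−r)
- Var(adjusted) = σ²(1−r²)
- Ratio = (1+r)/2

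If the SDs differ (σ₀ at baseline, σ₁ at 12 months), Var(change) − Var(adjusted) = (σ₀ − rσ₁)², which is never negative. Equal SDs therefore set the size of the gain, not its direction.

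**Step 3: power at 1050 patients in 50 clusters.** Column A scales the whole variance by (1+r)/2, so the residual ICC stays at 0.01. Column B is more cautious: adjustment reduces only the within-cluster part, and the between-cluster variance stays at 0.01 × 25.4². The variance multiplier in B is ((1+r)/2 − 0.01 + 0.2625)/1.2525, where 0.2625 = 0.01 × 1.25 × 21.

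| r | (1+r)/2 | Power, A | Power, B |
|---|---|---|---|
| planned model | 1 | 79.7% | 79.7% |
| 0.3 | 0.65 | 93.4% | 90.8% |
| 0.5 | 0.75 | 89.7% | 87.7% |
| 0.6 | 0.80 | 87.7% | 86.1% |
| 0.7 | 0.85 | 85.7% | 84.5% |
| 0.9 | 0.95 | 81.7% | 81.3% |

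Put as sample size, on basis A the planned power would be reached in 50 clusters with about 740 patients (r = 0.5), 858 (0.7) or 985 (0.9) instead of 1050.

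**Step 4: chance imbalance.** If the arms differ at baseline by d (intervention minus control) by chance, the unadjusted change difference shifts by −(1−r) × d. For an illustrative d of 3 points the shift is 1.5 (r = 0.5), 1.2 (0.6) or 0.9 points (0.7), which is 18% to 30% of the 5-point target. Given that imbalance and no true effect, two-sided rejection would be about 13%, 10% or 8%.

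The 3 points are an assumption. For scale, a change SD of 25.4 implies a score SD of 25.4/√(2(1−r)): 25.4, 28.4 and 32.8 at r = 0.5, 0.6 and 0.7. Ignoring clustering, the SE of a baseline difference is that SD × √(2/525), or about 1.6, 1.8 and 2.0 points. Three points is thus 1.5 to 1.9 SEs, which is on the large side for chance.

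**Step 5: simulation** (clustered data, r = 0.6, true effect 5, 1,500 runs, least-squares point estimates). With the intervention arm 3 points lower at baseline and the 12-month score regressing to a common mean, the unadjusted estimate averaged 6.2 and the adjusted one 5.0. Without imbalance, the empirical SEs were 1.78 and 1.62.

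**The case against.** The strongest reply is that the plan is coherent. The endpoint is a change, the SD and ICC used for sizing are those of a change, and the model analyses a change. The test delivers its stated power, and randomisation makes the estimator unbiased over chance imbalance. All of this stands. A reader might infer from the missing covariate that the trial is underpowered; Step 1 shows that it is not. Nor is baseline ignored, since it forms the outcome. The gain also depends on an unknown r, and at r = 0.9 it is only about 2 percentage points.

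A stronger reading is tempting: that recruitment after allocation creates baseline differences by selection, that the change score is biased by them, and that baseline adjustment removes the bias. The documents do not support it.
- Adjustment corrects chance imbalance, or selection that acts on the measured score itself. KCCQ-OSS is taken by telephone interview, whereas enrolment is completed at the practice, and nothing shows that recruiters see the score.
- If intervention practices enrolled patients whose scores are persistently 3 points lower, the change score would be unbiased, and the adjusted estimate would be off by (1−0.6) × 3 = 1.2 points at r = 0.6. The simulation assumes regression to a common mean, so it cannot settle which case applies.
- Consecutive identification limits selective enrolment, although it does not mask it.

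A reader might also infer that the secondary multivariable model excludes baseline KCCQ-OSS. Its covariates, "age, sex, NYHA functional class, time since diagnosis, care dependency, and living status", are given only as examples, so exclusion is not shown.

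**Conclusion.** The point holds as a matter of precision. The primary model leaves out a collected covariate that would narrow the confidence interval at no data cost. With equal SDs and residual ICC 0.01, power at 1050 patients in 50 clusters would rise from 79.7% to between about 82% (r = 0.9) and 93% (r = 0.3), and to 86% to 90% for r between 0.7 and 0.5. If the between-cluster variance is not reduced at all, the gain is up to about 2.6 points smaller. The direction holds for every r below 1 with equal SDs; the size rests on an r that the documents do not give.

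Adjustment also protects the estimate against a chance baseline imbalance, worth (1−r) times its size. It is not a remedy for selection after allocation. The planned analysis is valid and meets its own power target, so this is a recommended improvement and not an error that undermines the trial.

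**What to change.** Make the primary analysis a linear mixed model of 12-month KCCQ-OSS (or of the change, which gives the same group estimate once baseline is in the model) with fixed effects for group and baseline KCCQ-OSS and a random intercept for CP. Report the group-only change model as a supplementary analysis, so that the published specification remains visible. Adjust each secondary score that has a baseline measurement for its own baseline value, and name baseline KCCQ-OSS explicitly in the multivariable model.

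The cost is one documented change, with no new data and no change to sample size. Because the primary model is already published and recruitment closed in June 2025, the change needs a dated and justified amendment made before any outcome is compared by arm. Results places the last follow-up visit in June 2026 and reporting in September 2026.

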### Health economic evaluation

A cost-effectiveness analysis will be conducted to estimate the mean differences in costs and effects (e.g., QALYs) between the intervention and control groups. The incremental cost-effectiveness ratio (ICER) will be calculated as the difference in mean costs divided by the difference in mean effects, where applicable. Where one strategy is both more effective and less costly, or vice versa, dominance will be reported instead of an ICER. Effects will be assessed as non-monetary and aggregated appropriately according to the study objectives. Utility values for the calculation of QALYs (Quality-Adjusted Life Years) will be derived from data collected using the European Quality of Life Questionnaire (EuroQoL EQ-5D-5L) using the German value set [27]. Relevant cost parameters will be collected individually to maintain the internal validity of the economic evaluation.

To minimize bias due to recall inaccuracies, resource use data will be collected from the most reliable sources available rather than relying solely on patient self-report. Data on hospitalizations will be extracted from hospital discharge letters, which are systematically reviewed by a clinical expert to identify main diagnoses and relevant procedure codes (OPS), allowing individual-level derivation of Diagnosis-Related Groups (DRGs). The number of visits to cardiologists will be obtained directly from participating cardiologists. Telemonitoring equipment, as an additional resource specific to the intervention, will be continuously recorded via the eHealth platform, whereas additional activities of the HF-MPAs will be documented separately by the HF-MPAs themselves. Information on other healthcare utilization, including GP visits, medications, emergency services, rehabilitation stays, nursing care, and therapeutic services (e.g., physiotherapy, occupational therapy, and speech therapy), will be collected from patients using a questionnaire based on the validated FIMA instrument [28]. Data on care level, living situation, and employment status will also be obtained at baseline and at the end of the observation period.

Costs for non-physician staff, such as HF-MPAs, will be calculated based on existing EBM (Einheitlicher Bewertungsmaßstab) codes and an hourly rate. EBM codes refer to the standardized reimbursement system for outpatient services in Germany, assigning monetary values to specific medical procedures. The patient-related costs of the eHealth platform will be calculated. Drug costs will be estimated using average prices. Furthermore, unit costs for various resources will be derived from published cost estimates [29, 30]. To account for the clustered study design and potential confounders, mixed-effects regression models will be applied, with the intervention group as a fixed effect and clusters (CPs) as random effects. Trial data will be assessed for completeness, and appropriate methods will be applied to handle missing values depending on their extent and underlying mechanism. If data are considered missing at random (MAR), multiple imputation techniques may be employed. Uncertainty in the ICER estimates will be assessed using non-parametric bootstrapping (e.g., 1,000 replications), and results will be presented in cost-effectiveness planes and acceptability curves. Sensitivity analyses will explore the robustness of results to assumptions regarding cost structures, the timing of DMP-HI implementation, and data completeness. All health economic analyses will be conducted using StataSE 17.

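### The health-economic model is said to handle confounders but names only group as a fixed effect; the QALY model should include baseline EQ-5D-5L utility

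*Protocol article*

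**What the plan says.** All references are to the protocol article.

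- **Effect measure.** Health economic evaluation sets out to "estimate the mean differences in costs and effects (e.g., QALYs) between the intervention and control groups". The ICER is "calculated as the difference in mean costs divided by the difference in mean effects".
- **Utilities.** In the same section they are "derived from data collected using the European Quality of Life Questionnaire (EuroQoL EQ-5D-5L) using the German value set". The section gives no formula for turning utilities into QALYs.
- **Timing.** Data collection says that "patients are interviewed by telephone by trained staff to collect endpoints at baseline and 12 months". It is the only schedule the article describes for patient-interview endpoints. Table 1 lists EQ-5D-5L among the measures followed over time.
- **Model.** Health economic evaluation opens the model sentence with its purpose, "To account for the clustered study design and potential confounders", and continues: "mixed-effects regression models will be applied, with the intervention group as a fixed effect and clusters (CPs) as random effects". It lists no covariate.
- **Elsewhere.** For the clinical endpoints, Statistical methods says: "A multivariable mixed-effects model will secondarily adjust for potential confounders, e.g., age, sex, NYHA functional class, time since diagnosis, care dependency, and living status". Secondary outcomes also get univariable and multivariable models. The health-economic sensitivity analyses concern cost assumptions, when the DMP-HI starts, and missing data. None concerns baseline utility.

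**The concern.** The model sentence gives two reasons for its mixed model, clustering and confounding, and then specifies terms that serve only the first. A random practice effect absorbs between-practice variation. Group plus that random effect adjusts for no baseline difference between patients in the two arms.

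For QALYs this matters more than for most outcomes. When utility is measured at the start and end of one year and interpolated linearly, the starting utility is a component of the QALY and the intervention cannot change it. An analyst who follows the sentence as written would count a baseline difference between arms as QALYs gained or lost. The same analyst would keep between-patient variation that an already collected value could remove. Both effects reach the ICER denominator, the cost-effectiveness plane and the acceptability curve. The primary KCCQ-OSS analysis is not affected.

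**Working it through.** **The plan's own figures.** The article gives no figure for the QALY or ICER analysis. Its sample size supplies only the patient numbers used in step 4. Taking 1050 patients as 25 clusters of 21 per arm, with ICC 0.01 and the cluster-size variation of 0.5 read as a coefficient of variation, the design effect is 1 + ((1 + 0.5²) × 21 − 1) × 0.01 = 1.2525. A 5-point difference with SD 25.4 and 48 degrees of freedom then has 79.7% power, against 80% stated. That reproduces and does not bear on this point.

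**Assumed inputs, not in the article.** QALY = (u0 + u12)/2 over one year; equal utility variance σ² at both times; correlation ρ between them of 0.3–0.8, with 0.5–0.7 as the central range; utility SD 0.20–0.30; no deaths.

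**Step 1: shift from a realised imbalance.** If the arms differ by d in mean baseline utility and there is no treatment effect, the expected 12-month difference is ρd. The unadjusted QALY difference is then (d + ρd)/2 = d(1 + ρ)/2.

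**Step 2: variance.** Unadjusted: Var[(u0 + u12)/2] = σ²(1 + ρ)/2. Given u0: σ²(1 − ρ²)/4. The ratio of adjusted to unadjusted is (1 − ρ)/2.

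**Step 3: numbers** (individual level, cluster component ignored).

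| ρ | Variance ratio | SE ratio | Unadjusted CI width relative to adjusted | Shift for d = 0.02 |
|---|---|---|---|---|
| 0.3 | 0.35 | 0.592 | 1.69 | 0.013 |
| 0.5 | 0.25 | 0.500 | 2.00 | 0.015 |
| 0.6 | 0.20 | 0.447 | 2.24 | 0.016 |
| 0.7 | 0.15 | 0.387 | 2.58 | 0.017 |
| 0.8 | 0.10 | 0.316 | 3.16 | 0.018 |

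**Step 4: how large a chance imbalance is.** With 25 × 21 = 525 patients per arm, and the KCCQ design effect borrowed for utility, the SE of d is SD × √(2 × 1.2525/525). This is 0.0138 at SD 0.20 and 0.0207 at SD 0.30. At ρ = 0.6 an imbalance of one SE shifts the QALY difference by 0.8 × 0.0138 = 0.011 to 0.8 × 0.0207 = 0.017.

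**Step 5: simulation** (2000 runs, 50 clusters of 21, ICC 0.01, SD 0.25, ρ 0.6, no treatment effect, least-squares estimates).

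| | Unadjusted | Adjusted for u0 |
|---|---|---|
| Mean estimate | 0.00008 | 0.00001 |
| Empirical SE | 0.0160 | 0.0062 |
| Slope on the realised imbalance | 0.84 | 0.04 |

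The mean near zero shows that chance imbalance does not bias the unadjusted estimator. The SE ratio, 0.0062/0.0160 = 0.39, is somewhat better than the 0.447 of step 3. The reason is that the simulated practice effect is the same at both times, so u0 absorbs most of it. Step 3 is the safer guide.

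**The case against.** **The article condenses a fuller plan.** Covariate lists normally sit in a full protocol or health-economic analysis plan, and neither is shown. A reader might infer that the trial has ruled out covariates in the economic model. The text does not support that. The sentence states an aim of dealing with confounders, does not call the model univariable (as Statistical methods does for the primary analysis), and the example list of confounders is open. What remains is narrower: the terms the sentence does specify cannot achieve its stated aim, and the article names baseline utility nowhere as a covariate.

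**Bias.** A reader might infer that any baseline imbalance biases the ICER. That is too strong. Chance imbalance moves a single realised estimate but averages out over randomisations, as step 5 shows. Systematic bias needs recruitment that differs by arm. Results indicates that practices are allocated after signing the contract and before recruiting patients, so this is possible. Nothing shows that it happened, and Participants calls for consecutive identification.

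**The sizes rest on assumed inputs.** The article gives no utility SD, correlation, QALY formula or expected utility gain. A reader might infer that imbalance will decide the sign of the ICER; without an expected gain, that cannot be shown. Deaths matter too. All-cause mortality is an endpoint, and a patient who dies within the year does not fit the formula. Deaths would add variance that u0 probably explains poorly, so the 15–25% probably overstates the gain. This objection stands as a limit on the size. The direction does not depend on it.

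**Costs.** Baseline utility does not enter the cost difference mechanically. The mismatch does not by itself show a need to adjust costs for baseline cost, and none is asked for here.

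**Conclusion.** The point holds in limited form. The stated purpose of the health-economic model and its stated terms need to be reconciled, and baseline utility is the covariate to name for QALYs. Under linear interpolation, the model as written passes a realised baseline imbalance into the QALY difference at a rate of (1 + ρ)/2, that is 0.75–0.85 for ρ of 0.5–0.7. It also leaves a confidence interval about 2.0 to 2.6 times as wide as the adjusted one (1.7 times at ρ = 0.3). These figures assume equal variances, no deaths and no cluster component. The loss is one of precision and of conditional accuracy. It becomes systematic bias only if recruitment differs by arm. It is worth fixing because the value is already collected, but it concerns a secondary economic analysis.

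**What to change.** In the QALY model, state as fixed effects group, baseline EQ-5D-5L utility and the HF-MPA randomisation stratum, and keep the random CP effect. Refit this model in each bootstrap replicate used for the ICER, so that the plane and acceptability curve reflect the adjusted estimate. State the QALY formula alongside it, including how deaths are valued. If a full analysis plan already contains these terms, the sentence in the article only needs to be brought into line.

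No new data are needed. The cost is a rule for a few missing baseline utilities, for which the article already allows multiple imputation. The change should be recorded before the analysis; Results puts the last follow-up visit in June 2026. Adjustment removes only the part of a recruitment difference that baseline utility captures, so baseline characteristics should still be compared by arm.
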